**Conclusions:**

We believe this to be the first large pragmatic study comparing clinical outcomes during normothermic versus hypothermic bypass in complex open heart surgery in children. It is expected that this work will provide important information to improve strategies of cardiopulmonary bypass perfusion and therefore decrease the inevitable organ damage that occurs during nonphysiological body perfusion.

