In both adult and pediatric cardiac surgery, many of the detrimental effects of CPB on end organ dysfunction were previously believed to be mediated by activation of the inflammatory response [1,15]. One may expect that CPB-related systemic inflammatory response syndrome and multiorgan injury to be enhanced during normothermia, since most enzymatic processes occur optimally at 37°C. Supportive of this notion are clinical studies in adults [16] in which normothermic CPB (35°C-37°C) was associated with significantly elevated levels of inflammatory markers compared to hypothermic CPB (28°C-30°C). Consistent with this, previous animal data have shown that the inflammatory response is reduced by hypothermia [17,18]. However, a conflicting picture is emerging from research. Ohata et al [19] have demonstrated an attenuation of certain inflammatory mediators following warm systemic perfusion (34°C) compared to hypothermic perfusion (28°C). In a clinical study at the Bristol Heart Institute [10,20], normothermic (37°C) perfusion was also associated with attenuation of inflammatory mediator release in the postoperative period, compared to moderately hypothermic (32°C) and hypothermic CPB (28°C). In contrast, others have suggested that induction of a systemic response is not temperature dependent. Rasmussen et al have shown that the release of systemic inflammatory mediators after cardiac surgery in adults was independent of mild hypothermia (32°C) when compared to normothermia (36°C) [21]. A randomized controlled trial (RCT) in 66 children having open heart surgery, who were randomized to either moderate hypothermia (24°C) or mild hypothermia (34°C), found that neither the systemic inflammatory response nor organ injury were influenced by bypass temperature [22]. Eggum et al demonstrated that there were only minor differences in inflammatory marker concentrations between pediatric patients undergoing moderate (25°C) hypothermia and those with mild (32°C) hypothermia during CPB [23]. This evidence was supported by an RCT carried out at BRHC comparing warm (35°C-37°C) and cold (28°C) CPB on simple congenital cardiac malformations, which indicated that both whole body inflammatory response and myocardial reperfusion injury were similar between the 2 groups [24]. In addition, Caputo et al and Eggum et al demonstrated that normothermic CPB was associated with reduced oxidative stress compared with hypothermic CPB. Other researchers have studied the effect of the temperature of the cardioplegia during pediatric cardiac surgery [25,26]. Poncelet et al have taken this a step further by studying the effect of the temperature of the CPB in addition to the cardioplegia in an RCT on 47 children having cardiac surgery [27]. In this study, children were randomized to either mild hypothermia with cold crystalloid cardioplegia (CPB temperature 32°C, cardioplegia at 5°C) or normothermic with intermittent warm blood cardioplegia (CPB temperature 36.5°C). They found no significant difference in the cellular ischemic insult to the heart or in the early and late neurodevelopmental status of the patients. With conflicting evidence arising from clinical trials comprising relatively low numbers of patients and mainly simple cardiac surgery cases, it is difficult to establish whether the induction of a systemic response is temperature dependent and the impact this may have on clinical outcome. This warrants a larger study with clinical outcomes as primary endpoints.

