### Sample Size

#### Primary Outcomes

The geometric mean postoperative hospital stay in our institution is estimated to be 6.2 days, with standard deviation (on the logarithmic scale) of 0.4. A sample size of 100 participants per group would be sufficient to allow us to detect a clinically relevant 1 day or greater reduction in mean length of stay with 90% power, assuming a 5% level of statistical significance (2-tailed).

Using estimates for ventilation time and duration of inotropic support from our institution, a total sample size of 200 would also be sufficient to detect a 16% reduction in ventilation time (3 hours), and a 13% reduction in inotropic support (4.7 hours). All these differences represent clinically relevant reductions.

In an earlier RCT comparing the same 2 interventions carried out at our institution (Thermic-1), 59 participants were recruited. The primary outcomes for this earlier study were biochemical markers of organ injury, but clinical outcome data were also collected. For the current study (Thermic-2), 141 participants have been recruited. The clinical data from the 2 studies will be combined for assessment of the clinical outcomes, giving a total sample size of 200 participants for analysis.

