### Statistical Analyses

#### Plan of Analysis

Binary outcomes will be compared using logistic regression. Quantitative outcomes will be transformed if necessary to achieve approximately normal distributions and compared using linear regression and time to event variables will be analyzed using survival methods. Outcomes with repeated measures (longitudinal data) will be analyzed using mixed models, which allow for unbalanced data. Alternative correlation structures will be considered, and the sensitivity of the results to the choice of structure examined. Analyses will be adjusted for age group (stratification factor). All analyses will be carried out on the basis of intention-to-treat. Outcomes will be reported as effect sizes with 95% confidence intervals.

Specific morbidities are too infrequent for the study to be able to detect statistically significant differences between groups. Frequencies of these adverse outcomes will be tabulated, in line with guidelines for reporting adverse events in trials, and reported in accordance with International Conference on Harmonisation Good Clinical Practice guidelines.

The analysis of the microarray data for the gene expression study—including normalization, noise reduction, and analysis using, for example, unsupervised hierarchical clustering and relevance network analysis—will be performed using Genespring 7 software. Following determination of the gene expression profiles, bioinformatics data mining tools (Genespring 7) will be used to identify the gene expression profiles that are differentially significant and to cluster them by biological function. This is vital for generating hypotheses about their role. Predefined stringent criteria will be used to select candidate genes for validation; only genes with statistically significant differential expression will be considered. Patterns of change in signaling pathway networks will be explored.

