####  Subgroup Analyses

Effect estimates for the 2 study phases (Thermic-1 and Thermic-2) will be examined by adding relevant interaction terms to the models.

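### The pooled Thermic-1 and Thermic-2 analysis should include trial beside age group in its main models, and show the Thermic-2 estimate next to each pooled one

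*Protocol article*

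**What the plan says.** Three places in the protocol article bear on this.

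- **Sample Size, Primary Outcomes.** Thermic-1 is described as an earlier randomised trial of the same two interventions at the same institution, with 59 participants. Its primary outcomes were biochemical, but clinical outcomes were also collected. Thermic-2 recruited 141. The article then says: "The clinical data from the 2 studies will be combined for assessment of the clinical outcomes, giving a total sample size of 200 participants". The target of 100 per group is justified by a "1 day or greater reduction in mean length of stay with 90% power".
- **Statistical Analyses, Plan of Analysis.** The one adjustment named is: "Analyses will be adjusted for age group (stratification factor"). Trial is not mentioned there.
- **Subgroup Analyses.** "Effect estimates for the 2 study phases (Thermic-1 and Thermic-2) will be examined by adding relevant interaction terms to the models".

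So each child's trial is used in the plan, but in a subgroup analysis. It is not said to be a term in the main pooled models.

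**The concern.** Children were randomised within Thermic-1 or within Thermic-2, so trial is a stratum of the pooled data set just as age group is a stratum within Thermic-2. The plan's own practice of adjusting for the stratification factor would put both in the model. If average stay, ventilation time or inotrope duration differs between the trials, a model without trial treats that difference as noise and loses power.

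A second issue is what the pooled result represents. Of the 200 patients, 59 (29.5%) come from a trial whose clinical data already existed. The pooled estimate is a legitimate summary of both trials, but it is not fresh evidence independent of Thermic-1. A reader will want to see what the 141 new patients show, and the stated sample-size justification covers only the combined 200.

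**Working it through.** **Inputs from the article (Sample Size, Primary Outcomes).** Geometric mean stay 6.2 days; SD on the log scale 0.4; 1-day reduction; two-sided 5%; 100 per group; Thermic-1 n = 59; Thermic-2 n = 141.

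**Step 1: the plan's own figure.** A fall from 6.2 to 5.2 days is d = ln(6.2/5.2) = 0.1759 on the log scale. With 100 per group, SE = 0.4 × √(2/100) = 0.0566. Power = Φ(0.1759/0.0566 − 1.96) = Φ(1.149) = 87.5%. Exactly 90% would need 109 per group. The reduction detectable with 90% power at 100 per group is 1.04 days, so the gap from the stated 90% is probably rounding. It is a separate matter, and 87.5% is the baseline below.

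**Step 2: leaving trial out of the main model.** Let g be the gap in mean log stay between the trials that remains after age adjustment. With shares 59/200 = 0.295 and 141/200 = 0.705, the SD without a trial term is √(0.16 + 0.295 × 0.705 × g²). The article gives no value for g, so this is a range of assumptions:

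| Assumed g | SD without trial | Power without trial | Power with trial |
|---|---|---|---|
| 0 | 0.400 | 87.5% | 87.5% |
| 0.2 | 0.410 | 85.8% | 87.5% |
| 0.3 | 0.423 | 83.7% | 87.5% |
| 0.5 | 0.460 | 77.1% | 87.5% |

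On the ratio scale, gaps of 0.2, 0.3 and 0.5 mean stays about 22%, 35% and 65% longer in one trial than in the other.

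**Step 3: bias.** Without a trial term, bias equals g times the difference between arms in the share of patients from Thermic-1. With arms of 29 and 30 in Thermic-1 and 71 and 70 in Thermic-2, and g = 0.5, this is 0.5 × (29/100 − 30/100) = −0.005 log units, negligible against 0.176. Thermic-1's arm sizes are not given, so near-equal arms are an assumption.

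**Step 4: Thermic-2 alone.** With 70.5 per arm, SE = 0.4 × √(2/70.5) = 0.0674. Power = Φ(0.1759/0.0674 − 1.96) = Φ(0.651) = 74.2% (73.7% with the t distribution). The reduction detectable with 90% power is 1.22 days.

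**Step 5: the interaction.** The SE of the difference between the two trials' effects is 0.4 × √(4/59 + 4/141) = 0.124. Power for a difference of 0.176, the whole design effect, is Φ(0.1759/0.124 − 1.96) = Φ(−0.542) = 29%. Power of 80% needs a difference of about 0.35.

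**Step 6: dependence on Thermic-1.** The pooled statistic is z = √0.295 × z₁ + √0.705 × z₂, with z₁ from Thermic-1. If z₁ is already known, the two-sided type I error of the pooled test given z₁ is 2.0% at z₁ = 0, 4.7% at z₁ = 1 and 14.9% at z₁ = 2. These z₁ values are assumed; the article reports no Thermic-1 clinical result.

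**The case against.** Much can be said for the plan.

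- **Trial is not ignored.** A reader might infer that it is, or that the 141 children get no estimate of their own. The Subgroup Analyses section rules that out: it examines effects by study phase, and an interaction model conventionally carries a trial main effect and yields an estimate for each trial. This stands. What remains is that the main model is not said to contain trial, and the Thermic-2 estimate has no stated place beside the pooled one.
- **The covariate list may be fuller elsewhere.** An article condenses, and the article does not say that age group is the sole covariate. Fair, but it fixes the pooling and names the adjustment, so the stated model is the one to correct.
- **The interaction is not offered as permission to pool.** Nothing makes pooling depend on it. This stands. The 29% power is only a caution against reading a non-significant interaction as evidence that the trials agree.
- **The power loss rests on an unknown gap.** It does. The SD of 0.4 is an institutional figure and may already contain case-mix variation, in which case adding between-trial variance counts some of it twice.
- **Thermic-1's case mix is not documented.** The Background describes a trial at the same hospital "comparing warm (35°C-37°C) and cold (28°C) CPB on simple congenital cardiac malformations", and the Abstract frames the present work as "comparing clinical outcomes during normothermic versus hypothermic bypass in complex open heart surgery in children". It is tempting to conclude that nearly a third of the data are simple cases. The article does not identify that trial as Thermic-1 in the Background, and Thermic-2 itself admits defects of varying complexity, so the conclusion is an inference only.

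**Conclusion.** The point holds as a modest, easily remedied weakness. The stated main models for a data set pooled from two separately randomised trials name age group but not trial. The cost is precision: from nothing to about 10 percentage points of power (87.5% down to 77.1%) across assumed gaps of 0 to 0.5 in mean log stay, if 0.4 is the within-trial SD. With near-equal arms there is no material bias.

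The pooled result is not independent of Thermic-1, and the power of the design depends on pooling: 87.5% with 200 against 74.2% with 141. A reader might go further and infer an inflated false-positive rate. The documents do not support that. Averaged over Thermic-1's possible results the pooled test keeps its 5% level, unless the decision to pool was itself driven by those results, and nothing in the article shows that it was.

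**What to change.** 1. In the Plan of Analysis, state that every model fitted to the pooled data includes trial (Thermic-1 or Thermic-2) as a stratification factor alongside age group, and that pooled survival analyses are adjusted for or stratified by trial in the same way.
2. Report the Thermic-2-only estimate with its 95% CI beside each pooled estimate, and state that 141 patients alone give about 74% power for a 1-day reduction in stay.

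No new data are needed. The cost is one extra covariate, one further column of estimates and a less favourable stand-alone power figure in print. If the within-trial SD is 0.4, adding trial leaves the pooled power at 87.5% with 200 patients whatever the gap between the trials.

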#### Secondary Outcomes

This sample size will also be able to detect clinically relevant differences in secondary outcomes with 90% power. For full details, see Multimedia Appendix 1.

### Statistical Analyses

#### Plan of Analysis

Binary outcomes will be compared using logistic regression. Quantitative outcomes will be transformed if necessary to achieve approximately normal distributions and compared using linear regression and time to event variables will be analyzed using survival methods. Outcomes with repeated measures (longitudinal data) will be analyzed using mixed models, which allow for unbalanced data. Alternative correlation structures will be considered, and the sensitivity of the results to the choice of structure examined. Analyses will be adjusted for age group (stratification factor). All analyses will be carried out on the basis of intention-to-treat. Outcomes will be reported as effect sizes with 95% confidence intervals.

Specific morbidities are too infrequent for the study to be able to detect statistically significant differences between groups. Frequencies of these adverse outcomes will be tabulated, in line with guidelines for reporting adverse events in trials, and reported in accordance with International Conference on Harmonisation Good Clinical Practice guidelines.

The analysis of the microarray data for the gene expression study—including normalization, noise reduction, and analysis using, for example, unsupervised hierarchical clustering and relevance network analysis—will be performed using Genespring 7 software. Following determination of the gene expression profiles, bioinformatics data mining tools (Genespring 7) will be used to identify the gene expression profiles that are differentially significant and to cluster them by biological function. This is vital for generating hypotheses about their role. Predefined stringent criteria will be used to select candidate genes for validation; only genes with statistically significant differential expression will be considered. Patterns of change in signaling pathway networks will be explored.

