### Randomization

Participants will be randomly assigned in a 1:1 ratio to either the hypothermic group or the normothermic group. Randomization will be stratified by age: 1 month or younger, 1 to 12 months, and older than 12 months. Allocations will be generated by computer using block randomization with varying block sizes. The allocation sequence will be prepared in advance of the study by a statistician independent of the study team. If a participant’s surgery is unexpectedly rescheduled, he/she will retain his/her study numbers and randomized allocation. Access to the allocation will be via a password-controlled secure database. Randomization will take place as close to the start of surgery as possible.

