#### Secondary outcomes

Data will be collected to characterize the following secondary outcomes:

In-hospital mortality and morbidity rates will be recorded.Blood loss and transfusion requirements will be recorded.Preoperative and postoperative echocardiographic (ECG) findings will be recorded.Routine blood gas and blood test results will be recorded.Renal function will be measured by testing urinary albumin, urinary creatinine, retinal binding protein (RBP), N-acetyl-β-glucosaminidase (NAG), and neutrophil gelatinase-associated lipocalin (NGAL) [28-33]. All markers of renal damage will be measured preoperatively and at several time-points postoperatively.Cerebral function will be measured by testing for glial fibrillary acidic protein (GFAP), a serum marker of traumatic brain injury [34,35]. GFAP levels will be measured preoperatively and at several time-points mid- and postoperatively.Regional oxygen saturation of blood in the cerebral cortex will be measured at approximately 15-minute intervals during the operative period using near-infrared spectroscopy (NIRS).Neuropsychological development will be assessed using the NEPSY-II psychometric tool [36]. Neuropsychological assessments will be performed on patients aged between 3-16 years old, preoperatively and at 3 and 12 months postoperatively. These tests are intended as a tool to allow the assessment of both basic and complex aspects of cognition across the following 6 functional domains: attention and executive functions, language, memory and learning, sensorimotor functions, social perception, and visual-spatial processing.Cardiac tissue biopsies from heart tissue discarded during the surgical procedure and considered clinical waste will be analyzed for biochemical markers and RNA analysis on a subset of 32 patients. If available, 4 samples will be collected from each patient in this subset; 2 samples will be collected immediately after institution of CPB and a further 2 samples will be collected 10-15 minutes after reperfusion. Biochemical tests will be performed on the biopsies to determine the presence of a range of important proteins and metabolites, and transcriptional profiling by RNA extraction will be performed with the aim to help establish whether any genomic expression changes associated with hypothermia could be prevented by using normothermic techniques.

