## Discussion

### Principal Findings

While whole body cooling is still very much an integral part of pediatric cardiac surgery in the belief that it provides some degree of protection against a systemic inflammatory response and multiorgan damage, there is little evidence to demonstrate that this translates to improved clinical outcomes [22-24,31,43]. This may, in part, be due to the multifactorial nature of CPB; the clinical outcome of a patient is likely to be affected by factors including the complexity of the anatomical defect being corrected and the time spent on CPB as well as the temperature of the CPB. For instance, correction of a simple anatomical defect performed using hypothermic CPB may attenuate inflammatory responses and organ damage, however, additional time spent on CPB to cool and rewarm the patient [22-24] may offset or mask these effects. In addition, most RCTs investigating normothermia versus hypothermia do not report the length of time spent at the allocated temperature, although through randomization the times should be similar in the 2 groups. Clinically, it is not appropriate to specify how long the target temperature must be maintained since CPB time should be kept to a minimum and rewarming must commence on completion of the anatomical correction. In practice, this results in shorter, less complex operations that potentially only receive the intervention for a short time period, while the longer operations may be exposed to the intervention for a greater length of time. Furthermore, we do not know how long the target temperatures of either 28°C or 35°C-37°C need to be maintained for physiological responses to take effect. While it would be difficult to impose a specific length of time for treatment intervention due to the constraints and complexity of surgery, it may be useful to collect information regarding the length of time during which the target temperature was maintained and this should be considered in future study design.

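### Age group is the only covariate named for adjustment, although pre-operative values of several secondary outcomes are collected and would sharpen those analyses

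*Protocol article*

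**What the plan says.** The Plan of Analysis covers binary, quantitative, time-to-event and repeated outcomes, and then states: "Analyses will be adjusted for age group (stratification factor"). Age group is also the only stratification factor: "Randomization will be stratified by age: 1 month or younger, 1 to 12 months, and older than 12 months". The one further model term is study phase, which appears under Subgroup Analyses: "Effect estimates for the 2 study phases (Thermic-1 and Thermic-2) will be examined by adding relevant interaction terms to the models".

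For longitudinal outcomes the plan says: "Outcomes with repeated measures (longitudinal data) will be analyzed using mixed models, which allow for unbalanced data". It does not say whether the pre-operative measurement is a covariate, the first response, or left out.

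The Secondary outcomes section shows that these measurements exist. On renal function: "All markers of renal damage will be measured preoperatively and at several time-points postoperatively". On brain injury: "GFAP levels will be measured preoperatively and at several time-points mid- and postoperatively". On cognition: "Neuropsychological assessments will be performed on patients aged between 3-16 years old, preoperatively and at 3 and 12 months postoperatively". Table 1 also marks pre-surgery collection of routine blood gases and routine blood samples.

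**The concern.** When an outcome is measured before and after the intervention, its own earlier value is often one of the best predictors of the later one. If the model leaves it out, two things follow. Variation between children that was already present before bypass stays in the residual. Any chance difference between the arms at baseline also carries through to the estimate, in proportion to the baseline-outcome correlation.

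This matters more where numbers are small. Renal markers and GFAP came in by amendment after 52 of the 141 children had been recruited, and NEPSY-II is restricted to ages 3 to 16. At stake is the width of the confidence intervals for these secondary outcomes. The plan reports effect sizes with 95% intervals, so wider intervals than necessary are a real loss.

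**Working it through.** The plan gives no figure on this point to reproduce: no correlation or residual variance for any secondary outcome stands in the article, and the details of the secondary-outcome power calculation are in an appendix that is not shown. The correlations below are therefore assumptions, shown as a range.

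**Step 1: what the model conditions on.** As written, the terms are treatment and age group, with study-phase interactions for the subgroup analysis. The pre-operative value is not among them.

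**Step 2: effect of adding baseline.** Take a linear model at one post-operative time, with baseline and outcome on the same (transformed) scale. Let r be their correlation within age group. Relative to ignoring baseline:

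- variance of the treatment effect is multiplied by 1 − r²;
- interval width is multiplied by √(1 − r²);
- the equivalent sample-size multiple is 1/(1 − r²).

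| Assumed r | 1 − r² | Variance reduction | √(1 − r²) | Interval narrower by | Equivalent sample multiple |
|---|---|---|---|---|---|
| 0.3 | 0.91 | 9% | 0.954 | 5% | 1.10 |
| 0.5 | 0.75 | 25% | 0.866 | 13% | 1.33 |
| 0.7 | 0.51 | 49% | 0.714 | 29% | 1.96 |

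At r = 0 the gain is nil and the cost is one degree of freedom.

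**Step 3: size of chance imbalance in the amended markers.** If every child recruited after the first 52 contributed, 141 − 52 = 89 would have GFAP and renal data, or about 44 per arm. The standard deviation of the chance difference in baseline means is √(2/44) = 0.21 outcome SDs. An imbalance of that size moves the unadjusted estimate by r × 0.21, which is about 0.11 SD at r = 0.5.

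**Step 4: how the baseline enters matters.** The three possible uses are not equivalent:

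- Change from baseline has relative variance 2(1 − r). This is 1.4, 1.0 and 0.6 at r = 0.3, 0.5 and 0.7. At 0.5 it does no better than ignoring baseline, and at 0.3 it does worse.
- Baseline as a covariate has relative variance 1 − r², which is never above 1.
- Baseline as a first response with equal arm means has essentially the same precision as the covariate model.

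A mixed model with baseline as a response but unconstrained arm means may give up some or all of the gain, depending on the contrast reported.

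**The case against.** The strongest reply is that the sentence in the plan does not exclude other covariates. Committing to adjust for the stratification factor is correct practice. The article condenses a fuller protocol, and an analysis plan may say how baseline enters each model. A mixed model may already take the pre-operative value as its first response, in which case part or all of the gain in the table is already secured. This stands, and it limits the finding: the percentages apply only against an analysis that ignores baseline. It does not remove the point, because the stated covariate set, fitted as written, leaves baseline out, and Step 4 shows that silence on its role is not harmless.

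It is also true that baselines exist only in subsets. For GFAP and renal markers, the first 52 children presumably lack the post-operative values too, so conditioning on baseline should lose no more of them.

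A reader might go further and infer that the co-primary analyses lose precision as well, because the Discussion says outcome is likely to depend on "the complexity of the anatomical defect being corrected and the time spent on CPB", and that a complexity covariate would bring power for hospital stay back to 90%. The documents do not support this:

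- No section says that the planned procedure or a complexity grade is recorded before randomisation, and nothing shows that one exists for the 59 Thermic-1 children.
- No share of variance explained by complexity is given.
- The log-scale SD of 0.4 is not said to be net of age group, so age adjustment alone may already reduce it.
- The apparent shortfall is 87.5% power with 100 per group and ln(6.2/5.2) = 0.1759. It disappears for a reduction of 1.04 days, so rounding to one day could explain it.
- If the durations are analysed by survival methods, the linear variance formula does not carry over.

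**Conclusion.** The point holds as a matter of efficiency for the secondary outcomes that have a pre-operative value. The named adjustment set does not use data that are already collected. Against ignoring baseline, the gain is a 9% to 49% lower variance for correlations of 0.3 to 0.7, which are assumed; it is less where the mixed model already uses baseline as a response.

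It should not be read as an error that biases results. Under 1:1 randomisation, adjustment for age group alone is valid, and its confidence interval already allows for chance imbalance. For the co-primary outcomes there is only a conditional suggestion about complexity, with no claim about power.

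**What to change.** In the analysis plan, for GFAP, renal markers, routine blood gases and blood tests, and NEPSY-II:

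1. Include the outcome's own pre-operative value alongside age group, on the same transformed scale as the outcome. It may enter as a covariate, or as a baseline response with arm means constrained equal.
2. State how missing baselines are handled so that no randomised child with post-operative data is dropped. The constrained-response form does this directly.
3. Keep the age-group-only model as a sensitivity analysis.

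Optionally, since the article itself calls defect complexity prognostic, pre-specify a grouped complexity category for the co-primary models. It should use only information available before randomisation, and only if it can be coded blind to allocation in both Thermic-1 and Thermic-2. Do not adjust for bypass time: it arises after randomisation, and the Discussion notes that cooling and rewarming add to it.

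For the secondary outcomes the cost is a few sentences and slightly more modelling, with no new measurements. The optional complexity category would need coding work and a check of the Thermic-1 records.
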